### Ethics

This study was approved by Sichuan Regional Ethics Review of Committee on Traditional Chinese Medicine in June 2013 (No. 2013KL-013), and follows the principles of the Declaration of Helsinki (Version Edinburgh 2000). All participates are asked to sign the written informed consent before randomization. All patients will be informed and given enough time to decide whether they would sign the informed consent and participate in this trial or they will be given other treatment options if they are not willing to.

### Patients

#### Study population and sample size

This study focuses on women experiencing perimenopausal syndrome. According to the previous study by Guang’anmen Hospital, China Academy of Chinese Medical Sciences (results still unpublished), the improvement of Menopause Rating Scale (MRS) scores of the electro-acupuncture group and the sham acupuncture group were 6.5 and 2, respectively. The difference in scores between the two groups was 4.5, and electro-acupuncture was not superior to sham acupuncture. Accordingly, we assume that a difference within 4.5 indicates acupuncture is not inferior to Climen® treatment. Using a non-inferiority design, and assuming a power of 90%, an alpha value of 5%, and a population standard deviation of 10, a total of 206 patients will be needed in this study. Each group needs 103 patients (assuming a 20% dropout rate).

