**Figure 1 F1:**
[figure not shown]
**Trial flow chart.** CPA, cyroterone acetate; E_2_V, estradiol valerate. Climen® from Bayer Healthcare Company Limited (Guangzhou, China).

**Table 1 T1:** Trial processes chart

	**Baseline**	**Treatment phase**			**Follow-up phase**		
	**Week −1**	**Week 0**	**Week 4**	**Week 12**	**Week 16**	**Week 24**	**Week 36**
Patients							
Enrollment	×						
Informed consent	×						
Signed informed consent		×					
Medical history	×						
Physical examination	×		×	×			
Laboratory test	×			×		×	
Breast and gynecological ultrasound	×			×			
Randomization		×					
Expectation of acupuncture		×					
Intervention							
Acupuncture plus auricular acupressure treatment group (*n* = 103)			28 sessions of acupuncture				
Comparison							
Climen® control group (*n* = 103)			E_2_V 2 mg/day for days 1 to 11 and E_2_V 2 mg + CPA 1 mg/day for days 12 to 21				
Outcomes							
MRS		×	×	×	×	×	×
MENQOL		×	×	×	×	×	×
Average hot flash score during 24 hours		×	×	×	×	×	×
Serum estradiol, FSH and LH levels	×			×		×	
Patients’ satisfaction			×	×			
Trial evaluation							
Safety of acupuncture			×	×			
Cost–benefit analysis				×			
Reasons of drop-outs or withdrawals							×
Patients’ compliance							×
Adverse events							×
Medicine alliance							×

CPA, cyroterone acetate; E_2_V, estradiol valerate; FSH, follicle-stimulating hormone; LH, luteinizing hormone; MRS, Menopause Rating Scale; MENQOL, Menopause-Specific Quality of Life. Climen® from Bayer Healthcare Company Limited (Guangzhou, China).

These participants will be randomly assigned to two groups (AA treatment group and Climen® control group) through central randomization in a 1:1 ratio. The central randomization system will be used and performed by the Clinical Evaluation Center of China Academy of Chinese Medical Sciences in Beijing. Authorized researchers can obtain random numbers and group assignments by calling the central randomization service number or logging into the website to apply. This procedure assures that randomization will not be influenced either by the acupuncturist or the patients.

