Our study still has limitations. Firstly, the whole research period of this study is 37 weeks (1 week baseline, 12 weeks of treatment and 24 weeks of follow-up) and may increase the rate of patient drop-out. We therefore reduce the treatment demand after the first month of treatment and keep close contact with our patients via telephone calls, short messages, emails, and so forth, during the follow-up period, to decrease the drop-out rate. Secondly, the three centers of this study are in Chengdu, which is a capital city located in the southwest of China, and the patients we will include in this trial are mostly local residents. The population may therefore not represent the advantages of a multicenter study. Thirdly, participants assigned to the acupuncture group may have more opportunities for contact with their acupuncturists and build a good doctor–patient relationship rather than those of the control group, which may improve the therapeutic effect [44]. We will therefore keep close contact with patients in the control group by telephone, Internet, and so on, to decrease this potential bias. Meanwhile, it is difficult to blind patients after randomization due to the specificity of acupuncture. We therefore strictly conduct central randomization and appoint different people to perform therapy, measurement and statistical analysis.

Owing to a lack of solid evidence for effectiveness of acupuncture treatment on perimenopausal syndrome, this trial aims to clarify this issue by means of a multicenter randomized controlled large-scale trial.

In conclusion, the results of this trial are expected to confirm whether acupuncture is effective in relieving perimenopausal syndrome.

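### The 4.5-point non-inferiority margin comes from an electro-acupuncture-versus-sham difference and is tied to no effect of Climen, so meeting it cannot by itself show that acupuncture is effective

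*Protocol article*

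**What the plan says.** The section on study population and sample size gives the whole derivation. In an unpublished earlier study, MRS improvements in "the electro-acupuncture group and the sham acupuncture group were 6.5 and 2, respectively". The article continues: "The difference in scores between the two groups was 4.5, and electro-acupuncture was not superior to sham acupuncture". The next sentence draws the margin from this: "Accordingly, we assume that a difference within 4.5 indicates acupuncture is not inferior to Climen® treatment". The sample size follows, "assuming a power of 90%, an alpha value of 5%, and a population standard deviation of 10", with 103 women per group after a 20% dropout allowance.

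The trial has two arms, acupuncture plus auricular acupressure and Climen, and no sham or placebo arm. The Background and the Discussions describe the benefit of hormone therapy in words only; no MRS figure against placebo or sham is given. The Discussions also report that earlier trials found no advantage of acupuncture over placebo needles. The article nevertheless closes by saying that "the results of this trial are expected to confirm whether acupuncture is effective in relieving perimenopausal syndrome". The abstract and the opening of the Discussions express the same expectation.

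**The concern.** A non-inferiority margin has to be smaller than what the active control is known to achieve over placebo, and small enough to be clinically acceptable. The stated reasoning establishes neither.

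- **Wrong comparison.** The 4.5 points separate electro-acupuncture from sham. They say nothing about Climen, and electro-acupuncture is not the regimen tested here, which is manual needling plus auricular acupressure.
- **Non-significance read as unimportance.** The article treats a difference that did not establish superiority as one that may be given up. A non-significant result can come from imprecision; it does not show that 4.5 points is negligible.
- **No link to the control's effect.** Without a figure for Climen over placebo or sham, the reader cannot tell whether a margin of 4.5 preserves any of that effect.

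At stake is the trial's main conclusion. With no sham arm, any statement that acupuncture works must pass through Climen's known effect, and the plan does not supply that effect.

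**Working it through.** **Inputs, all from the sample-size section:** improvements of 6.5 (electro-acupuncture) and 2 (sham); margin 4.5; SD 10; power 90%; alpha 5%, sidedness not stated there; 103 per group; 20% dropout. A true difference of zero is assumed, because the article states none.

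**1. The margin.** 6.5 − 2 = 4.5. It is the entire point estimate of the earlier difference.

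**2. The plan's own sample size.** n per arm = 2 × [SD × (z for alpha + z for power) / margin]². At one-sided 5%: 2 × [10 × (1.645 + 1.282) / 4.5]² = 84.6, so 85. The t-based version gives 86, and 86 × 1.2 = 103.2, which is the stated 103 per arm and 206 in total. The plan's figure therefore reproduces at one-sided 5%. At one-sided 2.5% the same formula gives 104 evaluable per arm before dropout, which does not match.

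**3. What meeting the margin would imply.** Let C be Climen's advantage over sham and D the package's deficit against Climen, both in MRS points of improvement. The package's advantage over sham is C − D. Non-inferiority establishes D < 4.5, hence C − D > C − 4.5. That lower bound is above zero only if C is above 4.5. The article gives no value for C.

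**4. How often a sham-level package would pass.** If the package equals sham, then D = C. Evaluable women per arm: 103 × 0.8 = 82.4, taken as 82. Standard error: 10 × √(2/82) = 1.562. The probability of declaring non-inferiority is Φ[(4.5 − C)/1.562 − z], with z = 1.645 or 1.960. The values of C are assumptions.

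| Assumed C | (4.5 − C)/1.562 | One-sided 5% | One-sided 2.5% |
|---|---|---|---|
| 2 | 1.60 | 48% | 36% |
| 3 | 0.96 | 25% | 16% |
| 4.5 | 0 | 5% | 2.5% |
| 6 | −0.96 | 0.5% | 0.2% |

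More precision does not help when C is below 4.5. With all 103 per arm evaluable and C = 2, the figures rise to 56% / 43%, because the sham-level response then lies inside the margin and a larger trial is more likely to accept it.

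**5. The time point.** The statistical analysis section places the primary MRS assessment at week 16. Climen runs for three 28-day cycles, each ending in 7 tablet-free days, so the last tablet is on day 2 × 28 + 21 = 77. Week 16 is day 112, or 35 days later if tablets start at randomization. The C that matters is therefore the advantage remaining at that point, which may differ from the on-treatment advantage.

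**The case against.** The strongest defence is that this is a deliberate, disclosed design. The Discussions explain why an active drug was preferred to placebo needles, call the trial pragmatic and describe hormone therapy as the gold standard; the Background frames effectiveness as a comparison with it. If Climen's effect on the MRS is large, 4.5 may lie well within it. The closing sentence states an aim, not a result. All of this stands as a reason for choosing Climen as control. It does not supply the missing effect size or repair the stated rationale. Nor does condensation into an article explain the problem, since the derivation is given in full.

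A reader might infer several stronger points that the article does not support:

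- **That a sham-level response sits exactly on the margin.** This needs Climen to improve the MRS by 6.5, but that figure belongs to electro-acupuncture. If Climen did improve it by 6.5, a sham-level package would pass only at the alpha rate, and success would exclude a sham-level response. The inference would reverse.
- **That a known share of Climen's effect is given up, or that halving 6.5 or 4.5 yields a proper margin.** Both borrow the same electro-acupuncture data and say nothing about Climen.
- **That the sample size is wrong for its inputs.** It reproduces at one-sided 5%. With 82 evaluable per arm, power at 4.5 is about 89% at one-sided 5% and 82% at one-sided 2.5%; that gap comes from the choice of alpha, not from the margin.
- **That the earlier study had no hormone-therapy arm.** Only two groups are described; the article does not say there were no others.

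**Conclusion.** The point holds in this form: the margin's stated justification is invalid, and the article contains nothing that places 4.5 below Climen's effect on the MRS. It cannot be said that a sham-level treatment would pass, only that the plan does not rule it out. Its chance of passing depends on the unstated C: from 48% / 36% at 2 points down to alpha at 4.5, and below alpha beyond that. These probabilities rest on the assumed C, SD 10, 82 evaluable per arm and a normal approximation.

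With neither a sham arm nor a stated control effect, meeting the margin would support a bounded statement about the package against Climen. It would not by itself support a conclusion that acupuncture is effective. This should be corrected before analysis, because it determines what a positive result may be said to mean.

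**What to change.** Remove the argument that 4.5 points is acceptable because electro-acupuncture did not prove superior to sham. Then take one of two routes.

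1. **Re-justify the margin.** Base it on evidence for the effect of Climen, or hormone therapy generally, over placebo on the MRS at the primary time point. State the fraction of that effect to be preserved and why the remaining loss is clinically acceptable, and restate the power with the 206 women and the sidedness made explicit. The cost is finding evidence that the article does not contain. If the margin becomes smaller, the stated power falls, and restoring it would need more women in a trial already recruiting.
2. **Keep 4.5 and limit the conclusion.** A positive result would be reported as showing that the acupuncture plus auricular acupressure package is worse than Climen by less than 4.5 MRS points. The statements in the abstract, the opening of the Discussions and the closing paragraph that the trial will settle whether acupuncture is effective would be withdrawn. This changes wording only and needs no extra patients; the price is a narrower claim.

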### Statistical analysis

All data from this study will be analyzed by special analysts with SPSS 20.0 (IBM Corp., Armonk, NY, USA).

The tests of outcomes are based on the intention-to-treat population. Sensitivity analyses are performed for the primary outcomes (MRS measured 16 weeks after randomization) by replacing missing data with multiple imputations and lost observations carried forward using SPSS 20.0. Multiple imputations are calculated using the propensity score method. The MRS is used as a dependent variable in an analysis of covariance, with the groups as random factors, and with baseline MRS and age as covariates, to account for potential baseline differences. Adjusted mean treatment effects are given alongside corresponding 95% confidence intervals and *P* values. The same analysis method will be performed for all secondary outcomes.

In addition to the above analysis, we will perform an exploratory analysis to describe group means over time. We will calculate summary statistics to reveal whether the two groups are changing in a similar or different fashion. A two-sided test is applied for available data, and *P* < 0.05 is considered statistically significant.

There is one acupuncturist in each center to do all treatment, which probably introduces a clustering effect in this trial. We therefore calculated the intracluster correlation coefficient from the result of this trial and report the coefficient [28].

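### The figure of 103 per group with a 20% dropout allowance fits only a one-sided 5% alpha, while the analysis reports 95% confidence intervals; at that level unadjusted power after dropout is about 82%, not 90%

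*Protocol article*

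**What the plan says.** In the protocol article, under Study population and sample size, the margin is set in these words: "we assume that a difference within 4.5 indicates acupuncture is not inferior to Climen® treatment". The calculation is then described, for a non-inferiority comparison, as "assuming a power of 90%, an alpha value of 5%, and a population standard deviation of 10", with a total of 206. The allowance for loss follows: "Each group needs 103 patients (assuming a 20% dropout rate"). Neither the sidedness of alpha nor an assumed true difference is given.

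Under Statistical analysis, the MRS is analysed by covariance with baseline MRS and age as covariates, and "Adjusted mean treatment effects are given alongside corresponding 95% confidence intervals" and P values. That section does not say which interval limit is compared with the 4.5 margin. A later paragraph, which opens by introducing an exploratory description of group means over time, mentions two-sided testing at P < 0.05. No 90% interval and no one-sided test is mentioned anywhere.

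**The concern.** In a non-inferiority trial the sidedness of alpha and the level of the deciding interval are the same choice. One-sided 5% goes with a 90% interval; a 95% interval goes with one-sided 2.5%. The article gives an alpha of 5% in one section and a 95% interval in another. A reader cannot tell whether 103 was sized for the interval that will be reported.

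Two things are at stake. If the 95% interval decides, the chance of showing non-inferiority when the treatments are equal is lower than the article claims, and an inconclusive result could be taken for more than it is. And while the article leaves the level open, a result whose 90% interval clears 4.5 but whose 95% interval does not could be read either way.

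**Working it through.** **Inputs.** From Study population and sample size: margin 4.5, SD 10, power 90%, alpha 5% (sidedness not stated), dropout 20%, 103 per group. From Statistical analysis: 95% interval. Assumed, because the article gives none: true difference 0.

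**Formula.** Evaluable n per arm = 2 × (z_α + z_β)² × SD² / margin² = 2 × (z_α + z_β)² × 100 / 20.25.

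**Step 1: reproduce 103.**
- One-sided 5%: 2 × (1.645 + 1.282)² × 100 / 20.25 = 84.6, so 85 per arm (86 with the t distribution). Then 86 × 1.2 = 103.2, which gives 103 when rounded to the nearest integer. The usual correction gives 86 / 0.8 = 107.5, so 108.
- One-sided 2.5% (two-sided 5%): 2 × (1.960 + 1.282)² × 100 / 20.25 = 103.8, so 104 per arm (105 with t), before any dropout. With 20% dropout this becomes 104 / 0.8 = 130, or 104 × 1.2 = 124.8, so 125 with the simpler inflation.

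So 103 is either the one-sided 5% figure with dropout added as a multiple of 1.2, or, to within a patient, the one-sided 2.5% figure with no dropout added. Only the first agrees with the statement that 20% dropout is included.

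**Step 2: power after 20% loss.** 103 × 0.8 = 82.4, so 82 per arm. The standard error is 10 × √(2/82) = 1.5617, and 4.5 / 1.5617 = 2.881.

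| Decision level | Calculation | Power at 82 per arm | With t |
|---|---|---|---|
| One-sided 5% (90% interval) | Φ(2.881 − 1.645) | 89.2% | 89.0% |
| One-sided 2.5% (95% interval) | Φ(2.881 − 1.960) | 82.2% | 81.7% |

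For comparison, 103 evaluable per arm with no loss at all have 89.8% power at one-sided 2.5%.

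**Step 3: the dropout slip alone.** At one-sided 5%, the required 86 per arm have 90.4% power; the 82 actually left have 89.2%. The difference is about one point.

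**Step 4: what the planned covariate adjustment could return.** If SD 10 is the unadjusted SD, the residual SD is 10 × √(1 − r²), where r is the correlation between baseline and follow-up MRS. The article gives no value of r, so these are assumptions, at 82 per arm and one-sided 2.5%:
- r = 0: 82%
- r = 0.3: residual SD 9.54, standard error 1.490, Φ(3.021 − 1.960) = about 86%
- r = 0.47: residual SD 8.83, standard error 1.378, Φ(3.264 − 1.960) = about 90%

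**The case against.** The strongest reply is that the sample size is sound on its own terms. A non-inferiority test is naturally one-sided, 5% is a possible level for it, and on that reading 103 is recovered and power after dropout is 89.2%, which nobody would call materially different from 90%. This stands. A reader might infer from the mismatch that the sample size cannot be reproduced at all; that goes too far, because one-sided 5% with the 1.2 multiplier does produce it.

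Second, the article reports a 95% interval but never says that this interval decides non-inferiority, and the analysis plan is not at hand. That also stands, and it is why the 82% is conditional. The two-sided sentence adds little, since it sits in the exploratory paragraph. The 95% interval is the firmer evidence: it stands in the main paragraph, attached to the MRS effect, and it is the only interval level the article mentions.

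Third, the planned analysis adjusts for baseline, so an unadjusted 82% may understate power. This stands as well. A reader might infer a type II error of about 18% under the planned analysis; the article does not support that, because it gives neither the correlation nor a statement of whether SD 10 refers to raw scores, change or residuals. By the same token, the covariate gain cannot be used to defend the stated 90%.

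What the reply does not remove is the conflict itself. It saves the sample-size sentence only by choosing a level that the analysis section does not use.

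**Conclusion.** The point holds as a mismatch between alpha and interval level, with a small inflation slip beside it. No single reading satisfies the stated 90% power, the 20% dropout and the 95% interval together. At one-sided 5% the design has about 89% power after dropout but calls for a 90% interval. At the level implied by the 95% interval, 103 contains no dropout allowance and power after dropout is about 82%, some 8 points below the stated figure.

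The 82% rests on four conditions: the 95% limit is the one compared with 4.5, the true difference is 0, the SD is 10, and covariate adjustment brings no gain. A correlation of about 0.47 would bring power back to about 90%. Power under a true disadvantage for acupuncture would be lower, but the article assumes no such difference, so that is a sensitivity question and not part of this error.

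The slip does not bias the treatment estimate, and a 95% interval is the stricter of the two rules. The wording should be corrected before the data are analysed. It is no reason to call the trial unsound or to insist on more patients.

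**What to change.** Keep 206 patients and change the text in three places.

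1. In the sample-size section, state the one-sided alpha, and name the interval and the limit that will be compared with 4.5.
2. Restate power to match:
   - With the 95% interval already planned: one-sided 2.5%, margin 4.5, SD 10, true difference 0, 82 evaluable per arm, about 82% power unadjusted. Add that the baseline-adjusted analysis raises this by an amount that depends on the baseline to follow-up correlation, and give the value assumed and its source (for orientation, 0.3 gives about 86% and about 0.47 gives about 90%). Say whether SD 10 is before or after adjustment.
   - If one-sided 5% was intended: say so, justify it, use a 90% interval for the non-inferiority decision in the Statistical analysis section, and restate power as about 89%.
3. Correct the dropout inflation to n / (1 − 0.20).

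The cost is wording only. On the first option the headline power becomes less favourable; on the second, the more lenient level has to be defended. Holding 90% unadjusted power at one-sided 2.5% would take 130 per arm (260 in total), which is the alternative if the sponsor does not accept the restated figure.

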#### Inclusion criteria

According to the 2011 criteria of the International Menopause Society [20] and the 2001 criteria of the North American Menopause Society [21], women aged between 40 and 55 who meet the following conditions (Table 2) will be included in this study: menstrual irregularity in the past 12 months, or menstrual period off at least twice in the past 12 months, or amenorrhea 2 to 12 months; suffering any of the following symptoms – vasomotor symptoms (hot flashes, sweats), psychological symptoms (insomnia, migraine, irritability), or genitourinary symptoms (vaginal dryness, dyspareunia); serum follicle-stimulating hormone levels >10 units/L, or decline of estradiol after amenorrhea; and voluntarily participating in this study with a written informed consent form signed by themselves.

**Table 2 T2:** Eligibility criteria

**Inclusion criteria**	**Exclusion criteria**
• 40 to 55 years old	• Non-natural menopause (due to surgery, radiation, medication)
• Perimenopausal female (menstrual irregularity in past 12 months; or menstrual period off at least twice in past 12 months; or amenorrhea of 2 to 12 months)	• Use of HRT, SSRIs, vitamin E, or black cohosh in past 4 weeks
• Suffering any following perimenopausal symptoms: vasomotor symptoms (hot flashes, sweats), psychological symptoms (insomnia, migraine, irritability), or genitourinary symptoms (vaginal dryness, dyspareunia)	• Any contraindication of HRT (for example, family history of breast cancer, hysteromyoma, benign galactophore diseases, or ovarian cyst)
• Serum FSH level >10 units/L, or decline of estradiol after amenorrhea	• Unknown causes of vaginal hemorrhage
• Willing to receive treatment and sign consents	• Poorly controlled hypertension, diabetes mellitus
	• History of malignant cancer, mental disorders (including depression), thyroid diseases, diabetic neuropathy
	• Dermatosis (for example, eczema, psoriasis)
	• Serious heart, liver or kidney diseases
	• Coagulation defeats or use of anticoagulant medicine (for example, warfarin, heparin, and so forth)
	• Use of sedative or anti-anxiety drugs
	• Cigarette smoking, alcohol or drug abuse
	• Pacemaker or artificial joints
	• Pregnant women or women in lactation
	• Participation in other clinical trials

FSH, follicle-stimulating hormone; HRT, hormone replacement therapy; SSRI, selective serotonin reuptake inhibitor.

